## Abstract

**Background:**

More than one million people in Germany live with dementia. Most of these people are cared for at home in the family setting. Supporting and caring for people with dementia is time-consuming, and family carers often have high stress levels and are at an increased risk of becoming physically and mentally ill. Medical rehabilitation (rehab) helps to relieve family carers and provide them with strategies to cope with stress. The aim of this study is to improve the sustainability of a multimodal rehab program for family carers of people with dementia. Research question: can the effects of this rehab be maintained through telephone-based aftercare groups following the rehab program?

**Methods:**

A prospective randomized controlled longitudinal trial is performed. The intervention group (IG) participates in telephone-based aftercare groups; the control group (CG) receives treatment as usual. For evaluation, a mixed-methods approach is used. The effects of the intervention are quantitatively evaluated by written questionnaires at four measuring points (pre- and post-rehab, as well as 6 and 12 months after the end of rehab). Primary outcome: participation (IMET). Secondary outcomes: Depressive Mood State CES-D, General Complaints SCL-90-R, Subjective Quality of Life WHOQUOL-BREF, Social Support F-SozU, performance in different areas of life, single scales, and support offers (single items). The intervention process is evaluated through qualitative interviews and focus groups with regard to the acceptance of and satisfaction with the aftercare offered; in addition, a health economic evaluation is performed using the EQ-5D questionnaire. Rehabilitants are included in the study (*N* = 103 each in the IG and CG) who, accompanied by their family members with dementia, participate in the rehab measure in Ratzeburg. The IG participates monthly in 6 telephone aftercare groups over a period of 6 months. Typical stress situations are discussed and worked on.

**Discussion:**

Upon successful evaluation, the offer to participate in telephone-based aftercare groups can be firmly established in the participating rehab clinic. Through minor adjustments, the offer would also be suitable for carers of physically ill people and for non-nursing-specific rehabilitation indications.

**Trial registration:**

German Clinical Trials Register: DRKS00013736, May 14, 2018.

## Background

Currently, in Germany, there are 1–1.5 million people living with dementia, and it is expected that this number will increase to 3.0 million people by 2050 [1]. Worldwide, and particularly in Germany, the family remains the cornerstone of caring for the elderly [2], and carers, therefore, bear a large part of the responsibility for caring for and supporting people with dementia. More than two-thirds (70%) of people in need of care and who live at home are primarily cared for by partners and children [3]. Approximately half of those in need of care are people with dementia [4].

Supporting and caring for people with dementia is time-consuming and requires significant personal commitment and day-to-day management. Therefore, family carers of people with dementia often have higher stress levels than carers of the physically frail elderly [5, 6], and they are at an increased risk of becoming physically and mentally ill [5]. The development of the stress experience of family carers is complex [7]; the obviously non-cognitive symptoms of dementia, such as psychotic symptoms, depression and challenging behaviour, are of particular importance [8, 9]. Challenging behaviour refers to recurring behaviours that are perceived by the social environment as maladaptive and inappropriate to the situation (e.g., aggressiveness, irritability, anxiety).

To date, many psychosocial interventions have been developed that aim to improve the mental and physical health of family carers and reduce their stress experience [5]. These interventions vary in format (individual or group format) and content (psychoeducation, symptom assessment, problem-solving, skills training, stress management strategies, behavioural modification). A meta-analysis [10] concludes that individualized and structured multicomponent interventions are most effective. Against this background, particularly for carers of people with dementia, a rehabilitation (rehab) concept has been designed at a rehab centre in Schleswig-Holstein: family carers receive specific offerings that help them build up their strength resources, and they are trained to better meet the demands of caring for their relatives with dementia in their everyday lives. This program should enable improved participation in life and in the community. To facilitate access to the rehab, the dementia-affected family member can also be accommodated and supported in spatial proximity. Thus, on the one hand, the concept enables preservation of the contact opportunity between the carer and his family member with dementia; on the other hand, it allows the rehabilitants to concentrate fully on their therapies.

The rehabilitants (family carers) receive comprehensive, multi-professional therapeutic treatments, as well as other forms of relief, including individual and group psychotherapeutic sessions, medical visits, nursing training, ergo-, art-, music- and physiotherapy. Furthermore, the rehabilitants participate in autogenic training, progressive muscle relaxation and dementia-specific family carers training, as well as social counselling. The concept has been implemented since May 1, 2012 and, thus far, it is unique in Germany in this form. Funding for such a rehab project, at which the relatives can be cared for and brought along, has been assured by the German nursing reorientation law since January 2013. The costs for the person with dementia are covered by the health insurance of the rehabilitant. If there is a need for care, the nursing care insurance of the family member with dementia will proportionally take over the costs of the corresponding short-term or preventive care.

The current results of an observational study to evaluate the rehab program in Ratzeburg show clear and statistically significant changes regarding depression and general complaints, as well as the global quality of life of family carers at the end of rehab [11]. However, these effects were reduced to nearly baseline levels at the 6-month follow-up. Although these results confirm the basic efficacy of medical rehab in most indications after the end of the measure [12], they also show, like other studies in this field [13, 14], that these effects are not sustainable.

A time-limited rehab of usually 3 weeks is not sufficient in most cases to persistently stabilize the treatment’s success. Rehabilitation aftercare is a possibility to support the transfer of the learned contents to everyday life. Meanwhile, there are numerous aftercare programs that, based on the specific problem situations of rehabilitants, facilitate the transition from rehab to everyday life. Usually, they take place nearby at home at contracted outpatient facilities of the payers. However, against the background of the nursing and caring for the partner with dementia, utilization of usual aftercare programs is difficult to implement for family carers. This point is the start of the study project *Talking Time – REHAB as Aftercare*. It aims to support the transfer of what has been learned in rehab to the home environment through location-independent telephone-based aftercare groups, thereby consolidating the rehab effects. Telephone aftercare has been proven in practice. The 16 randomized, controlled trials found in a literature review suggest that telephone-based aftercare can increase the sustainability of rehab [15].

However, a wide variance in the underlying concepts was determined in the included studies. The strongest effects were obtained by concepts with the highest care intensity. Most of the included studies involved dyadic concepts. In contrast to existing studies, in Talking Time – REHAB, a group setting was selected for the telephone aftercare. With telephone-based aftercare in a small, professionally moderated group, a higher intensity of care can be assumed; therefore, a large sustainability effect can be expected. As part of the TALKING TIME project [16], for the first time in Germany, structured telephone-based support groups for carers of people with dementia were implemented. Talking Time – REHAB is formally based on the structure of the TALKING TIME intervention; however, the content is adapted to ensure the function of rehab aftercare.

### Study aim and research question

For the effect evaluation of this study project, the following primary questions and/or hypotheses arise:Does participation in the telephone-based aftercare groups lead to increased social participation by family carers of people with dementia?Can the health-related effects and competences obtained in multimodal rehab be maintained or even increased after rehab by participating in telephone-based aftercare groups?

The process evaluation of Talking Time – REHAB focuses on the following questions:What structures and processes contribute to the successful implementation of the aftercare offering?What promoting factors or hindrances influence successful implementation?How satisfied are the participants with the individual aspects of the aftercare offering?

## Methods

### Design

To investigate the long-term effects of telephone-based aftercare groups, a randomized controlled prospective longitudinal study is being conducted at one rehab centre. For the effect and process evaluation, in the sense of a mixed-method approach, both quantitative and qualitative methods are used [17]. Rehabilitants receive specific rehab for family carers of people with dementia and are randomized at the end of the measure. The randomization is performed externally by the Institute for Social Medicine and Epidemiology (ISE) of the University of Lübeck by generating a randomization list with the statistics program SPSS 22.0. After the rehab, at six appointments and in addition to the aftercare recommendations by the social worker, the intervention group receives telephone-based aftercare in groups, and the control group receives only the aftercare recommendations. The study design includes four measurement times: at the beginning (t0), at the end of the rehab (t1), 6 months after the end of the rehab (for the IG after completion of telephone-based aftercare groups) (t2) and 12 months after rehab ends (t3). Figure 1 represents the study flow.

**Fig. 1 Fig1:**
[figure not shown]
Study design

### Sample size calculation

As no studies in the field of nursing care have investigated the effects of aftercare in addition to a supportive intervention for carers, the sample size calculation for this study is based on the current results of the evaluation study on the effectiveness of the rehab program for family carers of people with dementia without aftercare (“standard care”), upon which this study project is based [11], and the results of a 2012 study of the impact of individualized aftercare on long-term rehab effects [18].

In the study with family carers, six months after rehab ended, the outcome parameter of participation, which was captured with the Index for the Measurement of Restrictions on Participation (Index zur Messung von Einschränkungen der Teilhabe, IMET [19]), showed that the rehab effect had nearly completely disappeared (ES = 0.06).

In the rehab aftercare study for the indication lower back pain, the same effect was observed for participation (IMET) in the CG [18], while the rehabilitants of the IG with individualized aftercare still showed an approximately medium effect size after 12 months (ES = 0.44).

Due to the consistently strong effects at the end of rehab in most recorded outcomes in the evaluation study for the rehab program in Ratzeburg, we expect for this controlled study, with telephone-based aftercare at the 6-month follow-up, an average effect of ES = 0.5 in the IG and a small effect of ES = 0.06 in the CG. Using a test power of 80% as the base, a two-sided t-test with an alpha error level of 5% requires a net group size of *N* = 82 each for the IG and CG. Based on experience with the current evaluation study of the rehab program in Ratzeburg and due to the high degree of loyalty of the rehabilitants to the rehab facility, we assume a moderate dropout rate of 20%. To evaluate *N* = 82 rehabilitants per group, initially, 103 participants per study group should be included. The rehab centre treats between 210 and 330 carers per year. The required number of cases can thus be achieved within the envisaged recruitment time.

### Recruitment of rehabilitants

All rehabilitants who in the course of a year, accompanied by a relative with dementia, consecutive newly admitted to AMEOS Rehab Clinical Centre Ratzeburg, a rehab clinic for family carers, will be addressed as potential study participants. Exclusion criteria are the presence of a personality disorder, psychotic symptoms, language barriers and cognitive impairments. The rehabilitants are first informed verbally about the study during an information event and asked to participate. Written information material will be handed out, and for those willing to participate, a written informed consent will be obtained.

### Intervention

#### Intervention group

The primary focus of the present study is the implementation of telephone-based aftercare, which is conducted in the form of aftercare groups. The structure of these groups is based on the support groups, as implemented by telephone in the TALKING TIME project [16]. The theoretical framework of these telephone rehab aftercare groups is provided using three approaches. 1.) According to Ruth Cohn’s theme-centred interaction (TCI) model [20], interaction and communication in a group are influenced by the factual, ego, and we-level. The factual level includes the theme of the telephone-based aftercare group to be discussed; the ego level focuses on the individual needs and current emotional state of each group participant; the we-level encompasses the group dynamic processes. To enable effective group work, these three levels must be in balance. Therefore, the role of the moderator is to keep these three levels in balance. This goal is completed by the moderator supporting the self-regulation of the group, strengthening the autonomy of the group members and creating an open atmosphere for communication and interaction. 2.) Based on systemic therapy [21], psychological burdens are considered not only at the individual level, but also, the systems of interpersonal relationships in which a person with dementia lives take centre place. The objective is to change these relationships and the interaction in different systems. In the context of people with dementia, this view can be briefly characterized by the concept of ‘dementia as a family disease’. Considered are the role changes, acceptance of new functions and changes in the relationship in general, the gradual farewell from a close relative, and the need to increasingly turn to that person because of the growing dependency. Also touched upon is the issue of ‘ambiguous loss’, that is, the person with dementia is still physically there but increasingly mentally absent [22]. 3.) From the broad spectrum of behavioural therapy, which understands psychological burdens as conditioned by learning experiences and as being changeable [23], the following principles take effect: a structured and transparent procedure, clear group structures, an emotion-, problem- and resource-oriented approach and support for self-help [21]. From the behavioural and systemic approaches, strategies and competences can be derived, such as how the family carer can better deal with ‘challenging behaviours’ in domestic everyday life. Communicating these skills is of particular importance when the aftercare recommendations target these challenging behaviours in everyday life.

The temporal and organizational procedure of the Talking Time – REHAB aftercare measurement consists of the following four components.**At the end of rehab – inclusion and preparation.** At the end of the rehab stay, a social worker, who is familiar with German social security statute book XI (Sozialgesetzbuch, SGB XI) and responsible for the moderation of the aftercare groups, compiles a portfolio of aftercare recommendations that are adapted to the individual situation of the respective family carer. These recommendations largely refer to possible strategies, as well as the individual situation of the carer, offering meaningful support but also providing recommendations for self-care in daily life, including nursing and supporting. The aftercare recommendations are discussed with the family caregivers at the end of rehab. In this discussion, the appointments of the telephone-based aftercare groups will be determined, and conversational rules for the groups are discussed. The rehabilitant receives a written checklist with all important information, including the conversation rules and the group folder (see below), to take home.**Reminder call**. The moderator calls each rehabilitant of the aftercare group 1 day before the next scheduled appointment. Such a reminder call lasts approximately 3–5 min and is necessary because, with a one-month interval of the aftercare group, the next appointment may be lost or forgotten by the participants.**Structured telephone-based aftercare groups**: Overall, the intervention provides for participation in six telephone-based aftercare group sessions within 6 months (every 4 weeks), each lasting approximately 60 min. The groups consist of a maximum of five caregivers and a moderator, who leads the group, and the groups are closed; the participants in a telephone-based aftercare group remain constant over the period of the six appointments. These groups are conducted as dial-out telephone conferences using a telephone computer system. The participants and the moderator are simultaneous automatically called by the telephone computer system and are connected to one another in the virtual conference room, after they have confirmed their personal receipt of the call by pressing the ‘1’ key of the dial pad of their telephone. In this manner, the telephone computer system confirms that an answering machine has not accepted the call. At the beginning of each group discussion, each participant gives a short update on his individual care and support situation and the status of the implementation of his aftercare recommendations. Afterwards, in all sessions, except for the first one, one of five themes will be introduced by the moderator: 1.) aftercare, implementation of the aftercare recommendations developed during the rehab; 2.) dealing with the relative with dementia; 3.) self-care (What am I doing for myself? When and where can I draw strength?); 4.) ambiguous loss, coping with grief and loss in dementia; and 5. social networks, perception and use of networks. To support the thematic introduction of each support group, each participant will receive a group folder developed particularly for the Talking Time – REHAB study, summarizing information on the themes of the Talking Time – REHAB sessions and including a checklist regarding technical issues (e.g., ‘what is the battery status of my telephone?’), which must be considered prior to each group session. The group folder can also be used as a workbook (e.g., for notes) during the support group meeting. This initial round, including impulse presentation, should take approximately 10–15 min. The remaining 45 to 50 min are available for the moderated exchange of experiences and the discussion between family carers. At the end of the group discussion, the moderator summarizes the content of each session. For quality assurance, the moderator is supervised by a psychological psychotherapist after the third and sixth session of the respective aftercare group.**Follow-up work of telephone-based aftercare groups**: Each group discussion is evaluated by each participant in writing. Before leaving the rehab facility, the participants receive a structured evaluation form for each aftercare group appointment. Using this form, family carers are encouraged to think about and evaluate each telephone group session (e.g., regarding the relevance of the topic of the session, open questions, helpfulness of the meeting, moderation of the group, well-being in the group or implementation of aftercare recommendations, etc.) The form is sent back to the moderator immediately after the telephone group session and provides the basis for the preparation of the next telephone group, but can also help in the sense of a formative process evaluation (see below, section on ‘process evaluation’) to optimize the behaviour of the moderator in the group situation. At the end of the intervention, as part of the summative process evaluation, all questionnaires will be sent to the ISE.

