### Data analysis

#### Effect analysis

For the effects analysis of the longitudinal data, analysis of variance with repeated measurements is used; for nominal and ordinal scaled parameters, contingency table analyses are used; and for subgroup analyses, chi-square tests and t-tests are used. The analyses are performed with SPSS 22.0 and complete cases will be analysed.

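### Intervention carers are treated in closed telephone groups, but the sample size and the repeated-measures ANOVA treat all carers as independent; with any positive within-group correlation the standard error is too small and the 80% power is overstated

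*Protocol article*

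**What the plan says.** - **Delivery (Intervention group section).** "The groups consist of a maximum of five caregivers and a moderator, who leads the group, and the groups are closed". Membership does not change: "the participants in a telephone-based aftercare group remain constant over the period of the six appointments". Each of the six sessions lasts about 60 minutes, of which 45 to 50 are moderated exchange between carers. Group dynamics are part of the stated theoretical framework.
- **Control (Control group section).** Carers receive individual aftercare recommendations that they put into practice alone. No group is formed.
- **Sizing (Sample size calculation).** The assumption is "an average effect of ES = 0.5 in the IG and a small effect of ES = 0.06 in the CG". The calculation is "Using a test power of 80% as the base", and "a two-sided t-test with an alpha error level of 5% requires a net group size of" 82 per arm. With "we assume a moderate dropout rate of 20"%, this becomes 103 per arm. No ICC, design effect or group allowance is given.
- **Analysis (Effect analysis).** "For the effects analysis of the longitudinal data, analysis of variance with repeated measurements is used", in SPSS and on complete cases. No telephone-group or moderator term is named.

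**The concern.** This is a partially nested design. Intervention carers share peers, a moderator and the course of their sessions; control carers share none of these. The article's own rationale is that carers in a group help one another, so some correlation of outcomes within a group is to be expected.

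A t-test treats every carer as an independent unit. A repeated-measures ANOVA allows for correlation over time within a carer, but not for correlation between carers in the same group. With positive correlation, the variance of the intervention-arm mean is understated. The naive test then rejects a true null too often, in either direction, and a correctly analysed trial has less than the stated 80% power. This touches the primary outcome (IMET). The Discussion would use a successful evaluation to establish the service permanently at the clinic.

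**Working it through.** **Inputs from the article.** Standardised difference 0.50 − 0.06 = 0.44; two-sided alpha 5%; power 80%; 82 evaluable per arm; 20% dropout; at most five carers per group; no grouping among controls.

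**Assumed, because the article gives none.** ICC of 0.01, 0.05 and 0.10.

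**Step 1: reproduce the plan.**
- n per arm = 2 × ((1.96 + 0.842)/0.44)² = 81.1, rounded up to 82.
- Power at 82 per arm is 80.4% by the normal approximation and 80.0% by the noncentral t.
- 82/0.8 = 102.5, rounded up to 103.

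The stated figures are recovered under full independence, so they contain no allowance for clustering.

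**Step 2: evaluable group size.** 103/5 = 20.6, so there are at least 21 groups. 82 evaluable carers over at least 21 groups is at most 82/21 = 3.9 per group on average. The calculations use m = 3.9 and m = 4.

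**Step 3: inflation.**
- Design effect in the intervention arm only: DE = 1 + (m − 1) × ICC.
- Variance inflation of the difference: V = (1 + DE)/2.
- Standard error: √((1 + DE)/82), against √(2/82) = 0.156 under independence.
- Type I error of a single-time-point comparison that ignores the groups: 2 × (1 − Φ(1.96/√V)).
- Power: noncentral t with the corrected standard error. Degrees of freedom are either 162 (ordinary t-test) or Satterthwaite, with 82/m − 1 for the intervention-arm variance and 81 for control.

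Example, m = 4 and ICC 0.05: DE = 1.15; V = 1.075; SE = √(2.15/82) = 0.162; 1.96/√1.075 = 1.890, so the type I error is 5.9%.

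| ICC | m | V | Type I error, groups ignored | Power, t-test df | Power, Satterthwaite df |
|---|---|---|---|---|---|
| 0.01 | 3.9 | 1.015 | 5.2% | 79.4% | 78.7% |
| 0.01 | 4 | 1.015 | 5.2% | 79.4% | 78.6% |
| 0.05 | 3.9 | 1.073 | 5.8% | 77.2% | 76.3% |
| 0.05 | 4 | 1.075 | 5.9% | 77.1% | 76.2% |
| 0.10 | 3.9 | 1.145 | 6.7% | 74.5% | 73.5% |
| 0.10 | 4 | 1.150 | 6.8% | 74.3% | 73.2% |

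The Satterthwaite degrees of freedom in these rows run from about 63 down to 53. Part of the loss in the last column therefore reflects how few groups inform the intervention-arm variance.

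**Step 4: can baseline adjustment offset the power loss?** Adjustment multiplies the residual variance by about 1 − r², where r is the correlation of baseline with follow-up. To cancel V = 1.15, r must be about √(1 − 1/1.15) = 0.36. The article gives no r. It does schedule IMET at baseline, so the adjustment is available.

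**The case against.** **The ICC is unknown.** This stands. At zero there is no bias, and at 0.01 the effect is negligible. Under a strict null in which the sessions change nobody's outcome, the sessions themselves create no correlation; it would have to come from who is grouped together, or from group effects that average to zero. A reader might infer that the type I error certainly exceeds 5%. The article does not support that certainty, only the conditional statement.

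**Groups of five overstate the effect.** This also stands. Taking m = 5 at ICC 0.10 gives a type I error of 7.4% and power of 72% with t-test degrees of freedom, and a reader might be tempted to cite those. But five is a maximum, and 82 evaluable carers over at least 21 groups average no more than 3.9. Those figures would need dropout to remove whole groups and leave the others full.

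**The type I figures are not for the planned test.** Correct. They apply to a comparison at one time point. For the ANOVA, the relevant ICC is that of the arm-by-time contrast, which cannot be derived from the article. The direction is the same if that ICC is positive.

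**Controls may not be fully independent.** Both arms share the inpatient rehabilitation, including group psychotherapy, and are randomised only at its end. If telephone groups are drawn from a single admission cohort, some of the correlation is shared with controls, and an intervention-only random effect could misstate the standard error. The article does not say how groups are composed. This is a caveat on the remedy, not a defence of assuming independence.

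**The detail may sit in a fuller document.** A separate analysis plan could add a group term. But the article does more than leave the matter open: it names the test behind N and names the effect analysis, and neither matches the way the intervention is delivered.

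**Conclusion.** The concern holds in conditional form. The sample size is fixed on independent carers, and the named ANOVA has no between-carer group term, while one arm is treated in closed groups. Any positive within-group correlation makes the standard error too small.

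For an assumed ICC of 0.01, 0.05 and 0.10, with about four evaluable carers per group or fewer and 82 per arm:

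- **Type I error, groups ignored:** about 5.2%, 5.8–5.9% and 6.7–6.8% for a single-time-point comparison.
- **Power allowing for clustering:** about 79%, 77% and 74% with t-test degrees of freedom, or 79%, 76% and 73% with Satterthwaite degrees of freedom.

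The loss is thus about 1 to 7 points of power. That does not invalidate the recruitment target, and baseline adjustment may recover the power. Adjustment alone does not cure the type I error; that requires the analysis to recognise the groups. The mention under Process evaluation of several moderators points to a possible further level of clustering, which is not counted here.

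**What to change.** 1. Record the assigned telephone-group identifier for every intervention carer and carry it into the analysis dataset. The Data management section describes only a three-digit participant number; without the group identifier the correct analysis cannot be run later.
2. Analyse IMET with a mixed model that has a random telephone-group effect in the intervention arm only, each control carer as a singleton, and small-sample (for example Satterthwaite) degrees of freedom. Analyse by the group assigned. Separate residual variances by arm are optional. State how telephone groups are formed, so that the singleton assumption for controls can be judged.
3. Beside N = 82, replace the single 80% with a power of about 73–79% over an assumed ICC of 0.01 to 0.10. State that the ICC is an assumption and that adjustment for baseline IMET may recover the loss.

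The cost is analysis-plan wording, one extra variable and a slightly less favourable stated power. No extra participants are needed, and the intervention does not change.
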